### Randomization

After providing verbal consent by telephone, those who are eligible will be allocated to one of four groups by a computer-generated randomization program using the SAS 9.2 statistical software (SAS Institute, Inc., Cary, NC, USA). The sequence will be generated by simple randomization. Participants will be subjected to different trial conditions depending on the number they are allocated.

### Statistical analysis

Compliance rates for FOBT screening will be compared among the four groups by a chi-square test. The satisfaction and intent to rescreen using a FOBT will be assessed by analysis of variance (ANOVA). The rates of positive FOBTs and the rates of advanced adenoma or cancer detected by colonoscopy using the different stool devices will also be analyzed by a chi-square test. The adjusted odds ratios (ORs) and 95% confidence intervals (CIs) of each outcome will be calculated using multiple logistic regression. All data will be analyzed using the SAS software, version 9.2 (SAS Institute, Inc., Cary, NC, USA).

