## Methods

### Trial design

The study will be conducted using a 2 × 2 factorial randomized control trial (RCT) design resulting in four groups. The first factor is the two methods of distributing stool devices (mailing vs. visiting a clinic), and the other is the two stool devices (sampling kit vs. conventional container). Thus, the study will be composed of four groups from two factors (allocation ratio1:1:1:1): (1) sampling kit received by mail; (2) conventional container received by mail; (3) sampling kit received at the clinic; (4) conventional container received at the clinic (control group) (Figure 1).

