### Sample size calculation

Study participants will be divided into two groups according to the method of receiving the stool-collection device. To determine the sample sizes of two groups, we will establish the null hypothesis (H_0_) and alternative hypothesis (H_1_) using the difference *p*_*1*_*-p*_*2*_, where *p*_*1*_ is the expected compliance rate in the group receiving collection devices by mail and *p*_*2*_ is the expected compliance rate in those receiving them at a clinic.$$\begin{array}{l} H_{0}:p_{1}=\;p_{2}\left(\delta =p_{1}-\;p_{2}=0\right)\;\text{vs}.\\ H_{1}:p_{1}>p_{2}\left(\delta =p_{1}-\;p_{2}>0\right) \end{array}$$

The expected compliance rate of participants visiting a clinic is based on that observed in 2010 by the NCSP, which was 30.8%, and the compliance rate of participants receiving stool devices by mail is estimated at 36% based on the assumption that the rate will be at least 5% greater.$$N=\frac{{\left\{Z_{\frac{\alpha }{2}}\sqrt{\left(r+1\right)\bar{p}\left(1-\bar{p}\right)}+Z_{\beta }\sqrt{rp_{1}\left(1-p_{1}\right)+p_{2}\left(1-p_{2}\right)}\right\}}^{2}}{r{\left(p_{1}-p_{2}\right)}^{2}}$$

Based on the above formula, 1,398 people will be needed in each group to detect the difference *p*_*1*_*-p*_*2*_ in the proportions using a two-tailed test and 80% power (1-β) at a 5% significance level. However, continuity correction tests will be needed to estimate very closely approximate values, and thereby a sample size of 1,438 in each group will be required. Finally, to allow for a 20% loss to follow-up, we will enroll an additional 350 participants per group, resulting in a final total for each group of 1,798 participants; thus, a total of 3,596 participants will be enrolled in the study.

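### The only test named for compliance is a four-group chi-square (3 df), but the sample size and its 80% power belong to the two-group mail-versus-clinic contrast (1 df)

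*Protocol article*

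**What the plan says.** Under Trial design the article states: "The study will be conducted using a 2 × 2 factorial randomized control trial (RCT) design resulting in four groups", with "allocation ratio1:1:1:1". It defines the factors separately: "The first factor is the two methods of distributing stool devices (mailing vs. visiting a clinic") and the type of device, sampling kit or conventional container.

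The Sample size calculation reduces this to one comparison: "Study participants will be divided into two groups according to the method of receiving the stool-collection device". Its hypotheses concern p1 (mail) and p2 (clinic) only. The requirement is set "using a two-tailed test and 80% power (1-β) at a 5% significance level". The clinic rate is the one "observed in 2010 by the NCSP, which was 30.8"%, and the mail rate is "estimated at 36% based on the assumption that the rate will be at least 5% greater". The resulting sizes per distribution group are 1,398 uncorrected, 1,438 with continuity correction and 1,798 after allowing for 20% loss, 3,596 in total. No device effect on compliance enters the calculation.

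The Statistical analysis section gives one test for compliance, the primary outcome: "Compliance rates for FOBT screening will be compared among the four groups by a chi-square test". It adds that adjusted odds ratios with 95% confidence intervals will be obtained for each outcome by multiple logistic regression. It does not list the model terms.

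**The concern.** A chi-square test on a table of four groups by complied/did not comply has 3 degrees of freedom. The hypothesis used for the sample size, p1 = p2, has 1. The same mailing effect faces a higher critical value on 3 df, so power falls.

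The omnibus test also answers a different question. It rejects equality of all four cells and does not attribute a difference to mailing, to the kit or to their combination. The factorial was built to separate the first two. A non-significant result could hide a mailing effect of the planned size, and a significant one would leave its source to be argued after the data are seen.

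This is not detail left to a fuller document. The article states a test, and it is not the one for which the trial was powered.

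**Working it through.** **Inputs.** From Sample size calculation: p2 = 0.308; p1 = 0.36, or 0.358 if the difference is exactly 5 points; two-sided α = 0.05; power 0.80; 1,438 evaluable and 1,798 enrolled per distribution group. With equal allocation, each distribution group holds two cells, giving 719 or 899 per cell. Assumption, because the sample size gives no device effect: mailing effect only, no interaction.

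**1. The plan's own figure.** The printed formula with r = 1 is

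N = {1.960·√[2p̄(1−p̄)] + 0.842·√[p1(1−p1) + p2(1−p2)]}² / (p1−p2)².

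- 35.8% versus 30.8%: p̄ = 0.333, N = (1.3063 + 0.5602)²/0.05² ≈ 1,394, and 1,434 with continuity correction. This is within 3% of the printed 1,398 and 1,438.
- 36% versus 30.8%: N ≈ 1,291, and 1,329 with correction. The printed N therefore fits a 5-point difference rather than the printed 36%. That is a separate matter, so both rates are carried forward.
- 1,438/0.8 = 1,797.5, rounded up to 1,798.

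The printed N is thus a two-group, 1-df calculation.

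**2. Power of the two tests on the same data.** With n per cell, the noncentrality is

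λ = n·Σ(pᵢ − p̄)² / [p̄(1−p̄)].

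For cells p1, p1, p2, p2 the sum equals (p1−p2)², and λ is the same for the 1-df marginal test and the 3-df four-group test. Only the critical value differs: 3.841 on 1 df, 7.815 on 3 df. Example: 719 × 0.05²/(0.333 × 0.667) = 8.09.

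| Rates | n per cell | λ | Power, 1 df | Power, 3 df |
|---|---|---|---|---|
| 35.8% vs 30.8% | 719 | 8.09 | 81.2% | 66.0% |
| 36% vs 30.8% | 719 | 8.74 | 84.0% | 69.7% |
| 35.8% vs 30.8% | 899 | 10.12 | 88.9% | 76.7% |
| 36% vs 30.8% | 899 | 10.93 | 91.1% | 80.1% |

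A simulation of the 36% case (200,000 replicates) gave 70.0% on 3 df and 84.2% on 1 df at 719 per cell, and 80.1% and 91.2% at 899.

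**3. What the four-group test would need.** Power of 80% requires λ = 10.90 on 3 df against 7.85 on 1 df, a ratio of 1.39. With a mailing effect only, that is about 1,938 evaluable per distribution group (about 3,875 in total) at 35.8%, or about 1,794 (about 3,588) at 36%.

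**4. Sensitivity to a device effect.** At 719 per cell, if the kit adds an assumed 3 points to compliance in both distribution groups, 3-df power is about 82% with 36% versus 30.8% and about 79% with 35.8% versus 30.8%. With an assumed 2 points and 36% versus 30.8% it is about 76%.

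**The case against.** The strongest reply is that the four-group test does not stand alone. The plan also provides adjusted odds ratios with confidence intervals for each outcome, and compliance is an outcome. A reader might infer from the four-group test that neither factor will be estimated. The article does not support that: a logistic model with a term for distribution method would both estimate and test mail versus clinic. What remains is narrower. The terms are not stated. The Study integrity section describes the groups as three interventions and one control, so the odds ratios could as easily be three groups against control. Nothing makes a factor contrast primary.

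Second, the power loss depends on the scenario. The kit is being tested because a gain is hoped for, and an effect of about 3 points would bring the four-group test to around 80% at 719 per cell. This stands, but the stated 80% rests on no device effect, and power gained this way is power to reject equality of four cells, not to show that mailing works.

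Third, the 20% loss may not apply. Compliance is defined as submitting a specimen within two weeks of receiving the device, so a non-submitter is an observed failure rather than a missing value. On that reading 899 per cell is the relevant size and 3-df power is 77–80%. This also stands, and it is why both sizes are shown.

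A reader might go on to compute power for single groups against control or for the interaction. The plan names no such tests, so those figures would not measure this discrepancy.

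**Conclusion.** Wrong as written. The sample size and its 80% power are for the 1-df mail-versus-clinic contrast, and the only test named for compliance is a 3-df comparison of four groups. With a mailing effect only, the cost is about 14–15 percentage points of power at the evaluable size and about 11–12 points if everyone enrolled is analysed. In that scenario the four-group test reaches 80% only with all 1,798 per distribution group and a difference of 5.2 points.

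These figures assume equal cells, no interaction and no device effect. The claim that the named test always has less than 80% power would go too far, since a device effect of about 3 points could close the gap. Two things do not depend on that assumption: the powered hypothesis has no test fixed for it, and the named test cannot say which factor acted.

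**What to change.** In Statistical analysis:

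- Name the mail-versus-clinic main effect (1 df, two-sided 5%) as the primary test of compliance, on all randomised participants, from a model with terms for distribution method and device.
- Report both main effects as risk differences with 95% confidence intervals; the planned adjusted odds ratios can stand beside them once their terms are stated.
- Show the interaction and the four cell rates as supporting results.
- Keep the four-group chi-square as a descriptive comparison.

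This changes analysis wording only; the data and the 3,596 participants stay the same. It should be settled before compliance is compared by group, so that the choice between omnibus and factor-level readings is not made after seeing results. The downside is that each main effect is averaged over the other factor, so it could mislead if the two interact. The cell rates and interaction must therefore appear next to it.

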**Illustrations of stool devices: (a) conventional container; (b) sampling kit.**

### Outcome measures

The primary outcome will be compliance with FOBT screening; compliance will be defined as the proportion of individual participants who submit stool specimens to the National Cancer Center within two weeks following receipt of collection devices. The secondary outcome will be participant satisfaction and intention to be rescreened in the next screening round as assessed by questionnaire at the clinic. The questionnaire will use a five-point Likert scale (1 = strongly disagree, 2 = disagree, 3 = uncertain, 4 = agree, 5 = strongly agree) with three dimensions: satisfaction with each process, from receiving stool devices to submission of specimens at the clinic; overall satisfaction with the entire process; and intention to be rescreened. The tertiary outcome will be the rates of positive FOBT results using sampling kits vs. conventional containers. Positive results are defined as those exceeding 100 ng/mL blood. All participants who undergo FOBT will be informed of the screening results via mail within three weeks, and those whose results are positive will be recommended to undergo colonoscopy. Colonoscopy or further biopsy for abnormal lesions will be performed by highly qualified colonoscopists upon provision of written consent at the NCC. Histopathological results will allow comparison of the detection rates of advanced adenoma or cancer between sampling kits and conventional containers. All outcomes of the study will be explained to respondents upon interview and prior to obtaining written informed consent.

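### Adjusted odds ratios from ordinary multiple logistic regression are promised for advanced adenoma or cancer detection, an outcome that may have too few events for a stable estimate or an informative null result

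*Protocol article*

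**What the plan says.** Under Outcome measures, after the tertiary outcome (positive FOBT rates by device), the article adds a device comparison of lesions found: "Histopathological results will allow comparison of the detection rates of advanced adenoma or cancer between sampling kits and conventional containers". Colonoscopy is offered only to participants with a positive test.

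Under Statistical analysis, "the rates of advanced adenoma or cancer detected by colonoscopy using the different stool devices will also be analyzed by a chi-square test". The next sentence says that adjusted odds ratios with 95% confidence intervals "of each outcome will be calculated using multiple logistic regression". No outcome is exempted, and the covariates are not listed.

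The trial is sized on compliance alone (Sample size calculation): "a total of 3,596 participants will be enrolled in the study". Clinic compliance is "based on that observed in 2010 by the NCSP, which was 30.8" per cent, and "the compliance rate of participants receiving stool devices by mail is estimated at 36" per cent. The document states no expected number of detections, and no positivity rate, colonoscopy uptake or yield.

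**The concern.** Detection sits at the end of a chain of submission, positive test, colonoscopy and lesion found. Each step shrinks the numbers, and the trial was not sized for the last one. Ordinary maximum-likelihood logistic regression has no finite estimate when all events fall on one level of a factor, and it is unstable close to that point. Adding covariates makes this worse.

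Two readings of the results are at stake. An adjusted odds ratio could be reported that is very imprecise or is an artefact of non-convergence. A non-significant comparison could also be taken to show that the two devices find lesions equally well. That would be a natural step, because the Background section rests the trial on the assumption that the device does not alter FOBT results.

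There is also a question of which groups are compared. The Background and Discussion sections expect the device to affect compliance. Submitters are therefore a group formed after randomisation, and a detection rate among them no longer has the full protection of the random allocation.

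**Working it through.** **Inputs from the document.** Enrolment is 1,798 per distribution route (1,438/0.8 = 1,797.5, rounded up) and 2 × 1,798 = 3,596 in total. Allocation is "allocation ratio1:1:1:1", so the two devices are balanced. Compliance is 36% by mail and 30.8% at the clinic. The document has no figure for detection to reproduce.

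**Submitters.** 1,798 × 0.36 + 1,798 × 0.308 = 1,201, or about 600 per device. If the 20% loss allowance is used up, 1,438 × 0.668 = 961.

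**Detections.** Events = submitters × positivity × uptake × yield. The last three factors are assumptions.

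| Positivity | Uptake | Yield | Total detections | Per device |
|---|---|---|---|---|
| 3% | 40% | 10% | 1.4 | 0.7 |
| 5% | 60% | 20% | 7.2 | 3.6 |
| 5% | 60% | 25% | 9.0 | 4.5 |
| 8% | 80% | 40% | 31 | 15 |
| 10% | 80% | 40% | 38 | 19 |

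**Chi-square and Fisher.** These figures come from exact binomial enumeration with 600 per device, at a nominal two-sided 5%. The last column is the approximate factor each way of an unadjusted 95% CI for the odds ratio, exp(1.96 × √(4/T)), where T is total events.

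| Total events | Chi-square size | Chi-square power, twofold difference | Fisher size | Fisher power | CI factor |
|---|---|---|---|---|---|
| 5 | 4.6% | 10% | 0.9% | 3% | 5.8 |
| 7 | 4.5% | 13% | 1.5% | 6% | 4.4 |
| 9 | 4.3% | 15% | 2.0% | 9% | 3.7 |
| 18 | 4.9% | 29% | 2.8% | 22% | 2.5 |
| 31 | 5.0% | 47% | 3.4% | 41% | 2.0 |

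Pearson's chi-square stays near or below its nominal size, because the two groups are almost equal. Precision is the weak point. At 9 events the risk ratio needed for 80% power is about 12; at 18 events it is about 4.4.

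**Logistic regression with device and route only.** There is no finite estimate if every event falls on one device or on one route. Treat the total as Poisson with mean m, spread evenly over the four groups:

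- A = P(at least one device has no events) = 2e^(−m/2) − e^(−m). The value for route is the same.
- B = P(both factors are one-sided) = 4e^(−3m/4)(1 − e^(−m/4)) + e^(−m).
- P(no finite estimate) = 2A − B.

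Results:

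- m = 5: 2 × 0.157 − 0.074 = 24%
- m = 7.2: 2 × 0.054 − 0.016 = 9%
- m = 9: 2 × 0.022 − 0.004 = 4%
- m = 18: below 0.1%

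**More covariates.** A simulation with device plus five assumed covariates (600 runs per setting) gave separation or a non-finite estimate in 41-45% of runs at 5 events, 10-13% at 9, under 1% at 18 and none at 31.

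**The case against.** The strongest objection is that sparsity cannot be proved from the document. The three rates that decide it are absent, and the assumed range is 27-fold (1.4 to 38). From about 18 events upward the logistic model behaves acceptably. The 30.8% is also a national programme rate, while these participants agree by telephone before randomisation and receive small gifts. If 70% submitted, positivity 5%, uptake 60% and yield 25% would give about 19 detections. This stands, and it makes the point conditional on the event count.

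A second objection is that the covariates are unlisted, and their choice and any fallback for small counts are commonly left to an analysis plan that is not shown. That is fair as far as the covariate list goes. But the article does name the method and applies it to every outcome, and the calculation shows that even a two-factor model can fail.

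A reader might also infer that the chi-square p-values are unreliable because expected counts could be below 5. The enumeration does not support this: the size is 4.3-4.6% at 5 to 9 events. Changing to Fisher's exact test would reduce power for a twofold difference from 10-15% to 3-9% over the same range.

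Finally, a reader might conclude that the rate among those tested should give way to yield per person randomised. The document does not support that either. The Background section asks whether the device changes test results, which needs a rate among people tested, and yield per person randomised mixes compliance with device performance. Each answers a different question. Nothing in the article says that a null detection result will be read as equivalence; the risk is one of interpretation.

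**Conclusion.** The point holds for the adjusted analysis and for the interpretation of the detection outcome. It does not hold for the chi-square test. At the planned compliance, with the middle assumptions (positivity 5%, uptake 60%, yield 20-25%), about 7 to 9 detections are expected in total. An ordinary logistic model then has no finite estimate in about 4-9% of trials with device and route alone, and in 10-13% at 9 events with device and five assumed covariates. Power for a twofold difference is 13-15%, and the odds ratio interval extends by a factor of about 4 each way. The instability disappears at around 18 events or more, but even at 31 events power is only 47%, so the caution about null results applies across most of the range. These sizes rest on assumed positivity, uptake and yield. Detection is a low-ranked outcome and the primary conclusion does not depend on it.

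**What to change.** For advanced adenoma or cancer detection only:

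1. Keep the chi-square test. Report the counts per device and the difference between devices with a small-sample 95% CI.
2. Replace ordinary multiple logistic regression with a Firth-penalised logistic model containing only device and distribution route.
3. State in the plan that a non-significant result is not evidence that the devices detect lesions equally.
4. Report yield per person randomised to each device alongside the rate among those tested, and say that the tested group is formed after randomisation.

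The cost is plan wording, standard software options and slightly more analysis work for a low-ranked outcome. The price is fewer adjustment covariates. Sample size, conduct and clinical management are unaffected.

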### Study integrity

This study will use a randomized study design to evaluate whether distribution using mail delivery and an improved stool-collection device increase FOBT screening compliance. Participants will be recruited through letters of invitation and randomly assigned to one of four groups (three interventions and one control group). Participants will be included only if they submit a stool sample to the NCC in person within two weeks after receiving a stool device, and these participants will be rewarded with small gifts. To maintain consistency in data collection, we will assign two well-trained research staff members to oversee data management, supervise all steps, and train assistant staff throughout the study duration.

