**Flow chart of the study.**

### Participants

Individuals aged 50 to 74 years living in Goyang will be recruited from February 2013 to February 2015. The National Cancer Center (NCC) in Goyang has sufficient resources to screen all NCSP recipients living in the Goyang urban area. The study will take place at the NCC Center for Cancer Prevention and Detection. Invitation letters including a brief description of FOBT screening and the purpose of the study will be mailed to target participants, and those who want to participate in the study will provide verbal consent via telephone. After study staff confirms that they meet the study criteria, eligible participants will be randomly allocated to one of four groups. Written informed consent will be obtained from all participants upon visiting the clinic to submit stool specimens within two weeks after receiving a stool device. Exclusion criteria include: a prior diagnosis with any cancer including colorectal cancer; a history of colonoscopy or polypectomy; or a history of a FOBT more recent than one year. Ethical approval has been obtained from the Institutional Review Board at the NCC (NCCNCS-12-683).

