### Data management

All information collected will be covered by the Personal Information Protection Act. Participants’ personal information such as name, identification number, and contact number will be not used until they have signed a consent form. Research staff will manage all information to ensure confidentiality under the personal data regulations. Participants’ identifiable data will be retained only until the end of the study. Any information will be eliminated upon participant request.

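### The Study integrity section includes only people who submit a stool sample, which is the primary outcome event itself and contradicts the rest of the design

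*Protocol article*

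**What the plan says.** All references are to the protocol article.

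- **Participants** and **Randomization**: people consent verbally by telephone, eligibility is confirmed, and then "eligible participants will be randomly allocated to one of four groups". No device has been handed out at that point.
- **Participants**: "Written informed consent will be obtained from all participants upon visiting the clinic to submit stool specimens". Only people who come back with a specimen therefore sign.
- **Outcome measures**: the primary outcome is "the proportion of individual participants who submit stool specimens to the National Cancer Center within two weeks following receipt of collection devices".
- **Sample size calculation**: expected compliance is 30.8% with clinic collection and 36% with mailing. Enrolment is raised from 1,438 to 1,798 per distribution group "to allow for a 20% loss to follow-up", giving 3,596 in total.
- **Statistical analysis**: "Compliance rates for FOBT screening will be compared among the four groups by a chi-square test".
- **Study integrity**: "Participants will be included only if they submit a stool sample to the NCC in person within two weeks after receiving a stool device". The same sentence adds that these people receive small gifts.
- **Data management**: of name, identification number and contact number, the text says that these and the "contact number will be not used until they have signed a consent form".

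**The concern.** The inclusion rule and the primary outcome name the same event (a specimen handed in), the same place (the National Cancer Center) and the same window (two weeks from receipt of the device). If the rule sets the analysis population, being analysed and being a success are the same thing, and compliance can no longer differ between groups.

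Partial application is also possible. Nowhere does the article say that all randomised participants are analysed, or that a missing specimen counts as failure. The window starts at receipt of the device. A clinic-arm participant must attend after randomisation to receive one, and someone who never attends has no receipt date. Such a person could be set aside as not included or as lost, and this could happen more in one arm than in the other. What is at stake is the protection that randomisation gives to the primary comparison.

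**Working it through.** **1. The plan's own sample size.** Inputs from Sample size calculation: two-sided 5% level, 80% power, equal groups. The printed formula with p1 = 0.36 and p2 = 0.31 (mean 0.335) is

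n = {1.960·√(2·0.335·0.665) + 0.8416·√(0.36·0.64 + 0.31·0.69)}² / 0.05² = 1,398.

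Continuity correction: (1,398/4)·{1 + √(1 + 4/(1,398·0.05))}² = 1,437.7, so 1,438. Loss allowance: 1,438/0.80 = 1,797.5, so 1,798, and 2 × 1,798 = 3,596. All four stated figures reproduce with the clinic rate rounded to 31%; the unrounded 30.8% gives 1,291 and 1,329. The rounding is a separate matter. What counts here is that the calculation assumes that 64% to 69% of each group do not submit and are nevertheless counted.

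**2. The inclusion sentence taken literally.** Expected submitters among those randomised:

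- mail: 1,798 × 0.36 = 647
- clinic: 1,798 × 0.308 = 554
- total included: about 1,201 of 3,596
- dropped: 3,596 − 1,201 = 2,395, or 66.6%

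Compliance among the included is 647/647 and 554/554, which is 100% in both distribution groups and likewise in each of the four cells. The difference is 0 and the pooled variance p(1 − p) is 1 × 0 = 0. The chi-square statistic and the odds ratios for compliance are then undefined.

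**3. If only the 20% were dropped.** Assume, for illustration, that 20% of an arm leave the denominator and that all of them are non-submitters. The observed rate becomes the true rate divided by 0.80: 36/0.80 = 45.0% for mail and 30.8/0.80 = 38.5% for clinic.

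| Dropped from | Mail | Clinic | Difference |
|---|---|---|---|
| nobody (as planned) | 36.0% | 30.8% | +5.2 pp |
| both arms equally | 45.0% | 38.5% | +6.5 pp |
| clinic arms only (extreme) | 36.0% | 38.5% | −2.5 pp |

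(pp = percentage points.)

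**4. Power with everyone retained.** At 36% against 30.8%, 1,798 per group gives about 91% power, and 1,438 gives about 84%. Keeping all randomised people in the denominator needs no larger sample.

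**The case against.** The strongest reply is that the article as a whole shows what was intended. Randomisation precedes submission, compliance is defined as a proportion, the planned rates are far below 100%, and a test of compliance rates is specified. The sentence just before the disputed one already calls people participants when they are recruited and randomised, and the disputed one goes on to gifts. A loose remark about who completes the study or receives a gift is a plausible explanation. This stands as an account of intent, and it is why the point is a contradiction in the text and not a design whose difference must be zero. It does not remove the need for a correction, because nothing in the article limits the sentence to gifts, the questionnaire or the test results.

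A reader might also infer that the 20% allowance itself removes non-submitters from the analysis. The document does not support that. The Sample size section only raises enrolment; it does not say who counts as lost or that anyone leaves the denominator. With 64% to 69% expected not to submit, the 20% cannot simply be the non-submitters. What remains is that, for an outcome in which not returning is failure, the allowance should not be open to that use.

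A reader might finally infer that the mailing effect would reverse sign. That needs every dropped person to be a non-submitter and every drop to fall in the clinic arms. No section says so, and equal dropping inflates the difference without reversing it.

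**Conclusion.** The Study integrity sentence is wrong as written and conflicts with the Participants, Randomization, Outcome measures, Sample size calculation and Statistical analysis sections. Followed literally, it makes compliance 100% in every group, leaves the primary test undefined and discards about 2,395 of 3,596 randomised people; the count assumes the planned rates of 36% and 30.8% and equal groups of 1,798. That is the consequence of the sentence, not a prediction of how the trial will be analysed.

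The figures for partial dropping (+6.5 pp if equal, −2.5 pp in the extreme case, against +5.2 pp planned) are illustrations. They rest on the assumptions stated with them and show only why the denominator has to be fixed in words. Confidence is high for the conflict in the text. The point should be settled before the primary outcome is analysed, because it decides who is in that analysis.

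**What to change.** 1. Delete the inclusion sentence in Study integrity, or restrict it to the questionnaire, positivity and colonoscopy outcomes and to the gifts.
2. State that everyone randomised after verbal consent is analysed for compliance in the allocated group, and that no specimen counts as non-compliant. Say explicitly that this covers clinic-arm participants who never collect a device and so have no receipt date; removing the sentence alone leaves them undefined.
3. State in Sample size calculation that the 20% allowance does not take non-submitters out of the primary denominator.
4. Align the consent wording in Participants with the data-use wording in Data management. At present only submitters sign, and personal information is not to be used before signature. The text should make clear that a non-submitter's allocation and outcome can be counted.

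Cost: items 1 to 3 are changes of wording, with no change to the sample size. Item 4 is a small further cost, because it touches the consent and data-protection text.
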